### Ethical Considerations

Ethical approval for this longitudinal surveillance system has been formally secured from the Medical Research Council of Zimbabwe (MRCZ/A/3191). The protocol strictly mandates that informed written consent is obtained from all participants prior to enrollment, ensuring that they fully comprehend the voluntary nature of their participation and their absolute right to withdraw without consequence. Confidentiality and privacy are strictly maintained through the use of unique participant identification codes and secure, encrypted data storage systems, ensuring no disclosure of personal details to third parties without express consent, unless legally compelled. Specialized consent procedures are in place for the collection and storage of blood and urine samples (both temporary and indefinite storage for future studies), as well as for the use of photographs, audio recordings, or video recordings. Participants diagnosed with clinically significant conditions (eg, hypertension or diabetes) are promptly referred to the nearest health facilities via prespecified referral protocols. Verbal autopsies follow international norms, requiring proxy consent from the next of kin.

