### Study Aims

This paper describes the establishment of a Zimbabwe HDSS to address critical NCD surveillance gaps through 4 specific aims:

Establish a longitudinal, population-based HDSS spanning rural and urban sites to generate accurate, timely data on demographic dynamics, NCD burden, risk factors, and health care access through continuous household surveillance with regular follow-up.Characterize prevalence, incidence, and temporal trends of major NCDs—hypertension, diabetes, cardiovascular diseases, and chronic respiratory diseases—with particular emphasis on identifying undiagnosed and untreated cases through active case-finding and objective biomarker measurement.Quantify rural-urban differences in NCD burden, risk factor exposure profiles, health care–seeking behavior, treatment access, and health outcomes to inform geographically targeted interventions and evidence-based resource allocation.Generate actionable evidence informing national NCD policy development, strategic planning, resource allocation decisions, and intervention design through systematic integration with existing health systems and continuous stakeholder engagement.

By addressing fundamental gaps in existing surveillance infrastructure, this HDSS will provide the continuous, geographically granular, longitudinal data essential for evidence-based NCD prevention and control in Zimbabwe’s rapidly evolving epidemiological landscape.

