### Data Collection Methods

Baseline and subsequent follow-up rounds will be conducted via structured, interviewer-administered surveys using REDCap tablet-based electronic questionnaires. These instruments have been developed by adapting core modules from the WHO STEPS [30] and the standardized DHS tools of the INDEPTH Network [20], ensuring alignment with established population-based surveillance practice. Household-level forms are linked to each HHID and capture location geocoordinates (imported directly from the mapping module), asset ownership, housing conditions, water and sanitation status, and records of vital events (births, deaths, and in- and out-migrations) since the last round. Individual-level forms are linked via a unique individual identification (INDID) nested within each HHID and address core sociodemographic factors (age, sex, marital status, education level, and occupation), women’s empowerment, and exposure to gender-based violence. Health-related modules capture self-reported history of NCDs (hypertension, diabetes, and cardiovascular disease), mental health status, and key communicable diseases (HIV, tuberculosis, and malaria), as well as reproductive health metrics. For each reported condition, data are also collected on prior diagnosis by a health professional, current treatment status, and type of medication, enabling estimation of the diagnosis-treatment-control cascade for key conditions. Behavioral risk factors assessed include tobacco use, alcohol consumption, dietary patterns, physical activity, and sexual behavior, with skip patterns and range checks built into the electronic tools to minimize data entry errors. All items are drawn from, or adapted directly from, WHO STEPS and INDEPTH Network instruments that have been widely used and validated in demographic and health surveillance sites in sub-Saharan Africa, supporting their reliability and suitability for this target population.

The household questionnaire additionally captures individual-level items on mobile phone ownership (personal or shared), primary connectivity mode (SMS, mobile data, or Wi-Fi), and internet access, providing a baseline characterization of digital access at the household and individual levels to contextualize NCD communication and service delivery in both rural and urban settings.

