### Follow-Up Procedures

Following the baseline census, longitudinal data collection rounds will be implemented annually over the 5-year surveillance period. Using the existing household and individual registers, field teams revisit each HHID and reverify the household roster, updating entries for births, deaths, in-migrations, out-migrations, and changes in marital status. Migration events are classified and dated using standard HDSS definitions, enabling calculation of person-time at risk and net migration rates. Migration events are identified and documented during each annual household roster update. New residents found in a previously mapped household who meet the standard residency criterion (at least 3 of the last 6 mo or intending to stay at least 6 mo) are classified as in-migrants, assigned a unique individual ID, and enrolled prospectively, with their origin and date of arrival recorded. Previously enrolled individuals confirmed by household members to have permanently departed the HDSS ward boundaries are classified as out-migrants, with their date of departure, destination, and reason for migration recorded and their follow-up record closed from that date, contributing person-time up to departure. Individuals who return after out-migration are reenrolled under their original ID, ensuring longitudinal continuity.

At each round, eligible adults are recontacted for updated interviews and measurements to estimate NCD prevalence and incidence, monitor changes in health-related behaviors and attitudes, and track risk factors over time. All recorded deaths are subjected to verbal autopsy using the WHO 2016 [31] standardized instrument administered on tablets; data are processed with automated cause-of-death assignment tools (eg, InterVA or InSilicoVA), given the limitations of vital registration in this setting.

Participant retention is managed through a structured recontact protocol whereby temporarily absent individuals receive at least 2 repeat visits at different times before being recorded as noncontactable for that round. At each round, the baseline characteristics of participants lost to follow-up will be compared with those retained to assess and account for potential attrition bias.

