### Data Analysis

The analytic plan encompasses descriptive statistics, robust prevalence and incidence estimations, and comparative analyses designed to quantify rural versus urban differences. Statistical software, primarily Stata (version 18; StataCorp LLC), will be employed. Numeric variables will be summarized using medians and IQRs, while categorical variables will be summarized using proportions. Logistic regression analyses (univariable and multivariable) will be used to identify and assess risk factors associated with NCDs, employing a hierarchical approach and stepwise backward elimination. The calculation of birth, mortality, prevalence, and incidence rates will be executed accordingly, and chi-square tests for trend will be used to analyze changes in NCD burden over time. Advanced statistical techniques, including regression and survival analyses, will facilitate robust estimation of NCD determinants and epidemiological transitions between the distinct study settings.

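### From the first follow-up round, the care cascade and the rural-urban contrast in treatment access mix the HDSS's own screening and referral with community change, and nothing shown separates them

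*Protocol article*

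**What the plan says.** Under Ethical Considerations, "Participants diagnosed with clinically significant conditions (eg, hypertension or diabetes) are promptly referred to the nearest health facilities". Follow-Up Procedures has field teams return to the registered households, and "At each round, eligible adults are recontacted for updated interviews and measurements to estimate NCD prevalence and incidence". The only newcomers described there are in-migrants to households already mapped.

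Data Collection Methods applies to baseline and follow-up rounds. For each reported condition it records prior professional diagnosis, current treatment and type of medication, "enabling estimation of the diagnosis-treatment-control cascade for key conditions".

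Aim 2 in Study Aims is to "Characterize prevalence, incidence, and temporal trends of major NCDs", "with particular emphasis on identifying undiagnosed and untreated cases through active case-finding and objective biomarker measurement". Aim 3 is to quantify rural-urban differences, including differences in access to treatment. Under Data Analysis, "chi-square tests for trend will be used to analyze changes in NCD burden over time". Strengths and Limitations discusses site selection, attrition, digital access, resources and self-report. It does not say that detection and referral by the HDSS can alter what later rounds find.

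**The concern.** An adult who was hypertensive and undiagnosed at baseline has been detected by the HDSS and referred. At the next round that adult counts as undiagnosed only if nothing came of the detection. In retained adults, diagnosis and treatment status at follow-up therefore depends partly on having taken part.

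The questionnaire item as described does not resolve this. Measurements are made by nurses or clinical research assistants, so a participant told of raised blood pressure by an HDSS nurse could truthfully report a professional diagnosis later without having visited a facility.

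Two results are at stake. An improving cascade could be reported as progress in the health system when some or all of it came from the study. The rural-urban contrast could also move if referrals are acted on more often in one site. The Introduction describes weaker rural infrastructure and treatment delays, and Study Setting describes better facilities in Bindura, so unequal uptake is plausible. Findings are to go to policymakers as briefs.

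**Working it through.** **Nothing to reproduce.** The article gives no figure for the screening effect. The check uses two of its numbers, both from Study Population and Sampling: baseline hypertension prevalence P = 30%, and the 2-point change between rounds (30% to 32%) that the study wants to detect. The second concerns overall prevalence and serves here only as a yardstick. The sample size attached to it is not used.

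**Assumed inputs, not in the article.**
- u, the share of hypertension undiagnosed at baseline: 0.3 to 0.7.
- L, the share of those who become diagnosed after HDSS detection and referral: 0.1 to 0.6.
- No other change between rounds, no new cases, and all adults retained unless stated.

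**Step 1: fall in undiagnosed prevalence.** Fall = P × u × L. At u = 0.5 the starting value is 0.30 × 0.5 = 15.0% of adults.

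| L | Undiagnosed at next round | Fall (points) |
|---|---|---|
| 0.1 | 13.5% | 1.5 |
| 0.2 | 12.0% | 3.0 |
| 0.4 | 9.0% | 6.0 |
| 0.6 | 6.0% | 9.0 |

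**Step 2: uptake needed for a 2-point fall.** L = 0.02 / (P × u).
- u = 0.3: 0.02 / 0.09 = 22%.
- u = 0.5: 0.02 / 0.15 = 13%.
- u = 0.7: 0.02 / 0.21 = 10%.

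**Step 3: dilution by adults not screened before.** If 30% of the second-round sample had never been examined (assumed), with u = 0.5 and L = 0.2, the fall is 0.70 × 0.30 × 0.5 × 0.2 = 2.1 points.

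**Step 4: effect on total prevalence.** If cases on treatment count as hypertensive, a new diagnosis leaves the total unchanged. If only measured raised pressure counts, and 40% of the newly diagnosed are controlled (assumed), the fall at u = 0.5 and L = 0.2 is 3.0 × 0.4 = 1.2 points. The article does not show the case definition.

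**Step 5: rural-urban contrast.** With u = 0.5 in both sites, L = 0.2 in one and L = 0.4 in the other would turn equal baseline values of 15.0% into 12.0% and 9.0%. That is a 3.0-point gap with no community change. The article supports at most the direction of such a difference; the two uptakes are purely illustrative.

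**The case against.** The strongest reply is that finding undiagnosed cases is itself the aim, and that detection with referral delivers it. This is largely right. A reader might infer that the article promises a trend in undiagnosed and untreated disease that it can never supply. The text does not support that. It promises trends in major NCDs, stresses identifying undiagnosed cases, and collects cascade data; a cascade trend is a fair inference and not a literal promise. Nor is such a trend out of reach. Baseline precedes any HDSS referral, and individual identifiers link the rounds, so adults who were positive and undiagnosed earlier can be flagged from data already planned. Linkage alone does not show whether a later diagnosis arose from the HDSS.

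A reader might also infer that the improvement would appear in the panel but not in the wards. That depends on which sampling statement governs. Study Population and Sampling describes both inclusion of all eligible adults and a systematic sample of households. Under full inclusion, panel and ward adults largely coincide; the change would be real there, and the problem becomes one of attribution.

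Large numerical claims about the bias or the rural-urban gap are also unsupported, because referral is not uptake and no uptake is given. The calculation also leaves out new disease over the more than two years between baseline (December 2024 and March 2025) and the first follow-up (second quarter of 2027).

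Finally, split reporting could sit in a full analysis plan that is not shown, and part of the article after its limitations was not available to check. This lowers the weight of the point. What stands is that the questionnaire as described does not record the source of a diagnosis, and the limitations shown do not mention the effect.

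**Conclusion.** The concern holds in a limited form. Follow-up results on diagnosis, treatment and control, and the rural-urban contrast in treatment access from the first follow-up round, would mix the HDSS's own screening effect with community change. Baseline estimates are unaffected, and total prevalence is little affected if treated cases count as cases.

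The direction is hardly in doubt: undiagnosed disease falls among adults already examined. The size is unknown. On an assumed undiagnosed share of 30% to 70%, modest uptake of about 22% down to 10% is enough to match the 2-point yardstick. Referral is not in question. The weakness lies in what is recorded and how later rounds would be read. It can be remedied cheaply while follow-up has yet to start.

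**What to change.** Leave referral unchanged.

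1. **Data Collection Methods, before the 2027 round.** Add to the follow-up form whether the condition was first identified at an HDSS visit, and the date of first diagnosis.
2. **Data Analysis.** Report follow-up cascade results separately for previously examined adults, labelled as *after HDSS screening and referral*, and for adults examined for the first time. Use the individual identifier to flag those who were positive and undiagnosed at an earlier round. State that the pooled change will not be read as a population trend in diagnosis or treatment.
3. **Strengths and Limitations.** State the screening effect, including that it may differ between sites.

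The cost is one extra item with its date, a split table and less precise subgroup figures. First-time examinees will be mostly in-migrants and earlier nonresponders, so their results are descriptive. Basing the population trend on them would replace a screening effect with selection bias. The changes work whether the HDSS enrols all adults or a sample of households.

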### Dissemination

The study findings will be disseminated through a multifaceted approach targeting diverse audiences. Results will be communicated to the scientific community via peer-reviewed publications and presentations at national and international academic conferences and workshops. Crucially, condensed policy briefs will be generated and distributed to national health authorities and policymakers to directly inform policy decisions. Community-level engagement will include feedback sessions, utilization of local media (eg, radio programs), and social media platforms to ensure accessibility of findings to the public. All study tools, standard operating procedures, and supplementary information will be included as annexes to maximize research transparency and reproducibility.

## Results

The Zimbabwe HDSS was granted ethical approval by the Medical Research Council of Zimbabwe on July 30, 2024. Community profiling and household mapping were completed in both sites in the third quarter of 2024. Baseline data collection was completed in Mt Darwin (rural site) in December 2024 and in Bindura (urban site) in March 2025. Data cleaning and quality assurance procedures for the baseline dataset were initiated in April 2025, and statistical analysis of baseline prevalence, risk factor distributions, and rural-urban comparisons is projected for completion by the first quarter of 2026, with findings expected to be submitted for publication by the end of 2026. The first annual longitudinal follow-up round is planned for the second quarter of 2027, subject to funding availability. Subsequent follow-up rounds are scheduled annually through 2029, with longitudinal incidence estimates, demographic event rates, and NCD trend analyses expected to be published progressively from 2026 onward.

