### Study Setting

The HDSS implementation will occur across 2 purposively selected districts within Mashonaland Central Province, Zimbabwe: Mt Darwin (rural site) and Bindura (urban site). Mt Darwin District encompasses approximately 1500 km^2^, hosting an estimated population of around 120,000 residents. The population predominantly relies on subsistence and small-scale commercial farming (eg, maize and tobacco), with sociodemographic indicators suggesting moderate educational attainment and agriculture-based household income. Health care services are provided by the Mt Darwin District Hospital and smaller rural clinics. Bindura District represents the urban setting, covering roughly 2800 km^2^ with an estimated population of 140,000 distributed across 14 wards. Bindura exhibits higher population density and a diversified economy, including mining (Bindura Nickel Corporation), trading, and academic communities linked to Bindura University. Health infrastructure is comparatively advanced, featuring the Bindura Provincial Hospital (a 200-bed referral facility) complemented by an extended clinic network. The HDSS will utilize 4 purposively selected wards (2 rural and 2 urban) to capture these socioeconomic and epidemiological contrasts.

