Within the 4 selected wards, all mapped households constitute the sampling frame, from which a systematic sample of households is drawn. Within each sampled household, all adults aged 18 years and older who meet the residency criterion are identified and invited to participate. Although the HDSS does not enroll every eligible adult resident because of resource constraints, this probability-based household sampling strategy, combined with formal power calculations, ensures that the resulting sample size is sufficient to address the primary study objectives. Using a baseline hypertension prevalence estimate of 30%, consistent with published data from Zimbabwe and comparable sub-Saharan African settings, a margin of error of ±2%, a 95% CI, and a design effect of 1.5 to account for household clustering, a minimum sample of approximately 3000 adults per site is required for robust prevalence estimation. This yields a total minimum analytical sample of 6000 adults across both rural and urban sites.

For the detection of a modest 2% absolute annual change in hypertension or diabetes prevalence (eg, from 30% to 32%) between surveillance rounds, with 80% statistical power and a 2-sided α of .05, a minimum of approximately 3500 participants per site per round is required. The estimated adult population across the 4 HDSS wards substantially exceeds this threshold, supporting the longitudinal objectives of the study. For rural-urban comparative analyses, equal allocation across the 2 sites provides 80% power to detect an absolute difference of 3% to 5% in key NCD outcomes. Subgroup analyses by sex, age group, and socioeconomic stratum are designated as exploratory, and appropriate corrections for multiple comparisons will be applied. Sample size calculations were performed in accordance with the WHO STEPwise approach to NCD risk factor surveillance (WHO STEPS) sample size guidance for population-based NCD surveys.

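### Baseline closed in different quarters at the two sites and the first follow-up is set for a third, so any seasonal variation enters the first measured change by a different amount at each site

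*Protocol article*

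**What the plan says.** The dates are in the Results section of the protocol article, and the Abstract agrees on the baseline and follow-up dates.

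- Mapping: "Community profiling and household mapping were completed in both sites in the third quarter of 2024".
- Baseline: "Baseline data collection was completed in Mt Darwin (rural site) in December 2024 and in Bindura (urban site) in March 2025". Only completion dates are given.
- First follow-up: "The first annual longitudinal follow-up round is planned for the second quarter of 2027, subject to funding availability". One window is named, with no split by site, and later rounds are annual through 2029.

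Both affected comparisons are planned. On the baseline round, Results says "statistical analysis of baseline prevalence, risk factor distributions, and rural-urban comparisons is projected for completion by the first quarter of 2026". Data Analysis names chi-square tests for trend for change over time. The targets are in Study Population and Sampling: "For the detection of a modest 2% absolute annual change in hypertension or diabetes prevalence (eg, from 30% to 32%) between surveillance rounds", and, between sites, "equal allocation across the 2 sites provides 80% power to detect an absolute difference of 3% to 5% in key NCD outcomes".

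Follow-Up Procedures says that rounds are annual but fixes no calendar months and does not say that the sites are fielded together. Future Plans calls the rounds biannual. Strengths and Limitations does not mention season or calendar timing.

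**The concern.** A rural-urban comparison is cleanest when both sites are measured over the same period. A change over time is cleanest when each round falls at the same time of year. The stated dates give neither in full.

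Study Setting makes seasonal variation plausible for some of the measured outcomes, because in Mt Darwin "The population predominantly relies on subsistence and small-scale commercial farming", while Bindura has a mixed economy. Diet, physical activity and weight may follow the farming year, and not equally at both sites. That blood pressure also varies with season is an assumption here, since the documents do not address it.

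If such variation exists, part of it would be read as a rural-urban gap at baseline, or as a secular change between baseline and 2027. It could equally hide a real difference. Because this is bias and not noise, a larger sample does not reduce it.

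**Working it through.** **1. Calendar check (dates from Results).**

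- Mt Darwin: December 2024 to April-June 2027 is 28 to 30 months, which is 24 months plus 4 to 6.
- Bindura: March 2025 to April-June 2027 is 25 to 27 months, which is 24 months plus 1 to 3.

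Counted from completion, neither interval is season-matched, and the offset is larger at the rural site. At baseline, fieldwork in Bindura ran to a close three months after Mt Darwin had finished, so the two sites do not share one measurement period.

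**2. The plan's own figures, for scale.**

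- Precision: 1.96² × 0.30 × 0.70 / 0.02² = 2017, and 2017 × 1.5 = 3025. This reproduces the stated 3000 or so per site.
- Smallest rural-urban difference detectable with 80% power at 3000 per site, from 30%: 3.4 points without the design effect and 4.1 points with it. Both lie inside the stated 3 to 5 points.

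**3. How large a seasonal shift would matter.** Assumptions, none from the documents: systolic pressure is normal with SD 18 to 22 mmHg, and the plan's 30% is treated as the share above a fixed cut-off of measured pressure. A mean shift d then changes prevalence by 1 − Φ(0.524 − d/SD) − 0.30.

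- With SD 20, shifts of 1, 2, 3 and 5 mmHg give +1.8, +3.6, +5.4 and +9.2 points.
- A 2-point change needs d = (0.5244 − 0.4677) × SD, which is 1.02, 1.13 and 1.25 mmHg for SD 18, 20 and 22.
- A 3-point change needs 1.5 to 1.9 mmHg.

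If cases are also counted through treatment, the effect is smaller.

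**4. If the fieldwork overlapped.** Suppose both sites began in October 2024 and measured evenly. Half of Bindura's six months would then coincide with Mt Darwin's three. If only the later half is shifted, a 2-point offset overall needs 4 points in that half: d = (0.5244 − 0.4125) × SD, or 2.0 to 2.5 mmHg.

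**5. Effect on the baseline site test.** Take 3000 per site and design effect 1.5 (effective 2000), with no true difference and a seasonal offset b. For b = 0.02, SE = √(0.30 × 0.70/2000 + 0.32 × 0.68/2000) = 0.0146 and b/SE = 1.37. The chance of a significant result is then about 28%. For offsets of 1 and 3 points it is about 11% and 53%, against a nominal 5%.

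**6. Effect on change over time.** The 2-point target is per year. Over 25 to 30 months, that rate gives 2 × 25/12 = 4.2 to 2 × 30/12 = 5.0 points. A 2-point seasonal offset would be 40% to 48% of it. For a linear trend at Mt Darwin, take baseline at month 0 and later rounds at months 29, 41 and 53 (May of 2027, 2028 and 2029, assumed). The mean is 30.75 and the sum of squares is 1548.75. A 2-point offset in the baseline alone moves the slope by 2 × 30.75/1548.75 × 12 = 0.48 points per year.

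**The case against.** The strongest objection is that only completion dates are stated. A reader might infer that the rural site was done first and the urban site a quarter later, so that site and season cannot be told apart. The documents do not support that. Mapping was finished at both sites in the third quarter of 2024, so both could have started together, and a month term could then be estimated over the shared months. This stands: the association is shown, but complete separation is not.

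Second, no passage shows that blood pressure, glucose or weight varies by season here, or in which direction. The millimetre figures convert assumed shifts into points and are not evidence of a shift. Nothing was computed for diabetes. This also stands.

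Third, a seasonal shift set against 2 points looks too large, because that target is annual and the first interval exceeds two years. This is correct, and step 6 uses the longer interval.

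Fourth, one window followed by annual rounds already suggests a common season. It does so only in part: no months or parallel fielding are fixed, and annual and biannual both appear.

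Fifth, a list of adjustment variables may sit in an analysis plan that is not shown. That is fair, and the lack of a month term is not by itself the point. The point rests on dates that the article does state. No later analysis can move a finished baseline, and adjustment helps only where dates overlap.

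**Conclusion.** The point holds as a design weakness that is cheap to limit. The first measured change is season-matched at neither site: from completion, it is off by about 4 to 6 months in Mt Darwin and 1 to 3 in Bindura. The baseline rural-urban contrast is at least partly tied to calendar period. Whether this produces material bias is unknown. Under the assumptions above, a shift of about 1 mmHg without overlap, or 2.0 to 2.5 mmHg with half overlap, would equal 2 prevalence points. The second-quarter date itself depends on funding.

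A reader might go further and conclude that the baseline contrast should give way to later rounds, or that the baseline should be left out of the trend. The documents do not support that. The bias is unquantified. Postponing the contrast would make it depend on rounds whose start is subject to funding, and dropping the baseline would leave at most three annual rounds over two years.

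**What to change.** - **Follow-Up Procedures:** state that every follow-up round is fielded at both sites in parallel, in the same calendar months each year, and reconcile annual with biannual.
- **Data Analysis:** keep the baseline in the rural-urban and trend analyses. Adjust for month of measurement where the sites' periods overlap. Add a sensitivity trend analysis restricted to the season-matched rounds from 2027 onward.
- **Reporting:** give fieldwork start and end dates by site. These will show how far the baseline periods overlap.
- **Strengths and Limitations:** name possible seasonal confounding of the baseline contrast and of the first-interval change.

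The cost is some constraint on scheduling and travel between sites, and a more cautious claim for the first interval. The scheduling rule needs to be set before the 2027 round, because a mismatch in that round would be hard to repair in the analysis.
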